## Abstract

Diabetic foot ulcer (DFU) is the leading cause of lower-limb amputations, with a significant impact on patients, families, and society. Since DFU medical treatments represent a major socioeconomic burden, cost-effective interventions are needed. This trial aims to assess the effectiveness of a muscle relaxation intervention compared to a hypnosis intervention versus active and passive control groups on DFU healing, physiological indicators of healing prognosis, and quality of life (QoL) in clinically distressed patients with a chronic DFU. A multicenter, randomized controlled trial with three assessment moments (baseline, two months post-intervention, and four months follow-up) will be conducted. Approximately 170 patients will be randomized and allocated to either treatment or control groups. Primary outcomes will be DFU healing, physiological indicators of healing prognosis, and QoL. Secondary outcomes will include perceived stress, psychological morbidity, and DFU representations. The efficacy of sessions on DFU healing will be qualitatively assessed in 12 patients allocated to the treatment and active control groups, as well as their family caregivers. This study will provide evidence regarding the effectiveness of two psychological interventions for the DFU healing process and the QoL of patients, with direct clinical relevance regarding DFU treatment and recurrence.

## 1. Background

Diabetes represents a growing public health concern with a growing global incidence during the last three decades [1] due to lifestyle changes and aging. According to the International Diabetics Federation, in 2021, an estimated 6.7 million adults have died as a result of diabetes or its complications. Over time, patients with diabetes have an increased risk of developing serious comorbidities, such as cardiovascular disease, blindness, kidney failure, and foot ulcerations [2].

Diabetic foot disease is one of the most serious complications of diabetes, impacting nearly 15% of all patients [3]. Diabetic foot ulcer (DFU) is a full-thickness wound below the ankle, in most cases, caused by poor glycemic control, calluses, ill-fitting footwear, underlying neuropathy, peripheral vascular disease, or improper foot care. Around 11–14% of worldwide patients diagnosed with diabetes will develop DFUs [4], which is the leading cause of lower-limb amputations in approximately 80% of these patients [5]. According to Zhang et al., the current DFU prevalence worldwide was 6.7%, while in Europe was 5.1% [6].

In addition to the devastating consequences of DFU development to patients and their families, the socioeconomic cost involved has become a burden. From 2007 to 2021, the direct cost of DFU treatment worldwide has increased from USD 232 to 966 billion, which reflects a dramatic increase. In Europe alone, the total medical costs for the management of DFUs in 2010 were estimated to be USD 105.5 billion, while in 2030, it is expected to reach USD 124.6 billion [2]. Thus, planning cost-effective interventions focused on DFU recovery becomes essential. This is also true regarding the impact on the environment, fewer trips to DFU clinics, fewer hospitalizations, and less clinical waste produced.

It is known that adherence to self-care behaviors and treatment is essential to wound healing. However, psychological factors, such as depression or anxiety, may also negatively influence DFU healing via psycho immunological effects [7,8]. Furthermore, DFU is associated with distress [9], and negative emotions contribute to prolonged infections, delayed wound healing, and poor quality of life (QoL), which is associated with low treatment responses and low remission rates, a major health concern [7,10,11].

Previous literature has emphasized the impact of stress on wound healing, almost exclusively in acute wounds, e.g., [12]. In fact, stress raises the level of cortisol, which has a negative impact on the immune system, particularly on wound repair due to immunity suppression [13,14]. By increasing the release of proinflammatory cytokines during tissue repair and driving tissue oxygen levels lower, psychological stress delays wound healing [15,16].

Stress may also impact the expression and function of microRNAs (miRNAs), important regulatory molecules that can be used as biomarkers for diagnosis or progression of complications from diabetes due to their ability to fine-tune cellular responses [17]. Thus, by modulating miRNA biogenesis, expression, and complex activity, stress can cause important changes in metabolism that may hamper DFU healing [18].

Glycemic control is one of the main strategies to monitor diabetes, reducing the complication of diabetes and the risk of hypoglycemia. Hemoglobin A1c (HbA1c) testing represents the best method to monitor glycemia in patients with diabetes, as it reflects levels of blood glucose over several weeks. Although distress has been associated with poor glycemic outcomes [19], the role of HbA1c in wound healing is not consensual. In fact, if some studies show direct associations between HbA1c levels and wound-healing rate, e.g., [20], other studies found no association between this biomarker and wound outcomes, e.g., [21].

Since there is evidence that psychological distress affects negatively wound healing [11], it is expected that reducing-stress interventions have positive implications on DFU recovery. Adjuvant interventions as relaxation training techniques have shown promising results in patients with diabetes [22,23] and patients with chronic DFUs [24,25]. Previous research also indicated hypnosis as an effective adjunct treatment in the management of diabetes, contributing to reduced blood glucose levels, better metabolic control, and increased blood flow to extremities, decreasing the risk of diabetic foot problems [26,27,28,29].

Although there is evidence suggesting the benefits of psychological interventions to patients with DFUs, the effectiveness of stress reduction interventions in DFU recovery, physiological indicators of wound healing, and patients’ QoL improvement has not been established. This is mainly because there are limited data evaluating the efficacy of psychological treatments in this area of research [30]. Thus, randomized controlled trials of low-cost psychological interventions to focus on the promotion of QoL and DFU healing are required. This paper describes the development of the PSY-DFU study protocol, which focuses on two interventions to reduce and manage stress and summarizes the advantages and limitations of this fully scripted treatment approach.

## 2. Methods

### 2.1. Objectives

The present study aims to:Assess the effectiveness of a muscle relaxation intervention with guided imagery (TG1) compared to hypnosis with guided imagery (TG2) versus a neutral guided imagery placebo (ACG) and a group that does not receive any psychological intervention (PCG) regarding DFU healing, physiological indicators of healing prognosis, and QoL in patients with clinical distress and a chronic DFU.Understand the perspectives of patients and family caregivers on the efficacy of TG1 and TG2 interventions versus ACG sessions for DFU healing.

#### Primary Specific Aims

The primary specific aims of this RCT are: (i) to compare the impact of both treatment groups (TG1 and TG2) in regard to DFU healing, physiological indicators of healing prognosis (biochemical parameters, inflammatory and angiogenic markers, miRNAs, and immune cells), and QoL, compared to control groups; (ii) to compare patients pre and post-intervention in the TG1 and TG2, controlling for patients’ health literacy, clinical characteristics (e.g., duration of diabetes and DFU, type of diabetic foot), and sociodemographic variables (e.g., gender, age, education, socioeconomic level); and (iii) to compare the efficacy of TG1 and TG2 versus ACG to DFU healing, according to participants and their respective family caregiver’s perceptions.

### 2.2. Study Design

The current study is designed as a longitudinal, participant-blinded, sham-controlled, cluster randomized controlled trial (RCT) with a nested qualitative evaluation. The RCT study includes three-assessment periods over the course of six months, while the nested qualitative study involves an additional semi-structured interview two weeks after completing the treatment or placebo sessions.

The protocol for this RCT is based on the Standard Protocol Items: Recommendations for Interventional Trials (SPIRIT) 2013 Checklist [31] (Table 1). The study design and flowchart of the protocol, following the CONSORT 2010 standards [32], are summarized in Figure 1. The study will be conducted in three major hospitals in the North of Portugal with multidisciplinary diabetic foot consultations, and was approved by the Ethics Committee of the three hospitals. The study is also registered on the ClinicalTrials.gov platform since the 7th of January 2021 (Registration number: NCT04698720).

### 2.3. Participant Recruitment and Selection Criteria

Patients with chronic DFU attending the first consultation of the multidisciplinary outpatient clinical of diabetic foot ulcer from three major hospitals in Northern Portugal will be recruited. In the first consultation, researchers (Researchers 1, 2, and 3) will collect the clinical information of each patient to signalize those that meet eligibility criteria. Patients will be consecutively enrolled in the study.

The inclusion criteria are: (i) being 18 years old or more, (ii) having one or two diabetic chronic ulcers (a non-healing ulcer for six or more weeks and less than 12 weeks; in case of patients with two active chronic DFUs, the ulcer with the largest area will be selected as the index ulcer) at the time of baseline assessment, (iii) reporting clinical levels of psychological distress, and iv) providing written informed consent. Clinical distress is assessed according to the Hospital Anxiety and Depression Scale (HADS) [33] and the Perceived Stress Scale (PSS) [34], with patients scoring ≥11 on the HADS subscales or ≥13 (male patients) and ≥17 (female patients) on the PSS evaluated as being clinically distressed.

Exclusion criteria include: (i) the DFU, at the time of baseline assessment, being a relapse; (ii) having three or more DFUs at the time of baseline assessment; (iii) having undergone a transplant; (iv) being on hemodialysis treatment; (v) having a cancer disease; (vi) having degenerative dementia or severe psychiatric illness (e.g., schizophrenia), (vii) receiving psychological counseling, or (viii) taking psychiatric medication during the study period.

For the qualitative study, participants that completed at least 75% of the intervention sessions or placebo sessions (active control group) will be invited to participate, together with their family caregiver. Participants will be purposively selected according to the type of diabetic foot (neuropathic versus neuroischemic) and DFU progression (positive versus negative). The sample will also be selected according to participants’ capacity to provide in-depth and rich-textures information regarding the intervention’s effectiveness since qualitative purposive sampling is considered to be more efficient than random sampling [35]. Thus, the quantitative study sample will include four single-per-participant interviews per group (4 conditions × 3 groups), in a total of 12 patients’ interviews and 12 caregivers’ interviews.

### 2.4. Randomization

All eligible patients will be randomly assigned to one of the four groups—TG1, TG2, ACG, or PCG—in varying size blocks so that, over time, all groups can have a similar number of participants [36,37]. An independent researcher (Researcher 4), unaware of the numeric coding for each group, will create the randomization sequence using an online random number generator (https://www.graphpad.com/quickcalcs/randomize1/, accessed on 15 December 2021) with a 1:1 allocation, using random block sizes of 12. Researchers 2, 3, and 4 are blind to the block size used in the randomization procedure.

A priori stratification was defined considering the three hospitals where data collection will take place, as well as two common comorbid conditions deemed as factors of poor prognostic outcomes in patients with DFUs, specifically chronic kidney disease (CKD) and peripheral arterial disease (PAD) [38,39], to ensure that distribution of patients between groups is balanced in terms of confounders. Thus, randomization is stratified according to (i) hospitals; (ii) CKD and its disease stages (without CKD/CKD stage 1 and 2/CKD stage 3 and 4); and (iii) PAD (without PAD/with PAD), in a total of 12 possible strata.

Participants’ blinding will be maintained throughout the conduct of the trial, whereas Researchers 1, 2, and 3 will be aware of the allocation since they are responsible and will conduct the TG1 and ACG sessions. Quantitative data analysts will be blinded to participant allocation. The randomization process will be conducted at the end of each week to reduce the time interval between the randomization and the beginning of interventions.

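### Section 2.4 contradicts itself on block size and who is blind to it, and leaves one unblinded screener (Researcher 1) off the blinded list

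*Protocol article*

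**What the plan says.** **Screening.** Section 2.3 of the protocol article says that "researchers (Researchers 1, 2, and 3) will collect the clinical information of each patient to signalize those that meet eligibility criteria". It adds: "Patients will be consecutively enrolled in the study".

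**Knowledge of allocations.** Section 2.4 says that "Researchers 1, 2, and 3 will be aware of the allocation since they are responsible and will conduct the TG1 and ACG sessions".

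**Blinding to block size.** Section 2.4 says that "Researchers 2, 3, and 4 are blind to the block size used in the randomization procedure". The same section gives Researcher 4 the task of creating the randomization sequence.

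**Block size.** Section 2.4 first says that patients are assigned "in varying size blocks so that, over time, all groups can have a similar number of participants". It then describes the sequence as made "with a 1:1 allocation, using random block sizes of 12".

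**Strata and timing.** Randomization is stratified by hospital (three), chronic kidney disease (three levels) and peripheral arterial disease (two levels). The section gives the number of strata as 12. Randomization is run at the end of each week.

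**The concern.** In blocked randomization, someone who knows the block size and the allocations already made in a stratum can work out which arms are under-represented in the current block. The usual protection is to keep block sizes from everyone who screens or enrols. All three screeners here know the allocations, so that protection carries weight.

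As written, it is misplaced. Researcher 1 screens and is unblinded but is not on the blinded list. Researcher 4 has no stated screening role but is on it, although blocks of a given size cannot be built by someone who does not know the size. A single fixed size is also easier to infer or exploit than randomly varying sizes, and the section says both.

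If a screener can anticipate the next arm, a borderline patient might be admitted, declined or deferred accordingly. Bias of that kind enters before baseline and cannot be reliably removed in the analysis. Some eligibility items leave room for this, such as the date the ulcer began (for the window of 6 to under 12 weeks) and whether the ulcer counts as a relapse.

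**Working it through.** The plan gives no figure for predictability, so there is none to reproduce. The check has two parts.

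**1. The roles side by side**

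| Researcher | Screens (2.3) | Knows allocations (2.4) | Builds the sequence (2.4) | Stated blind to block size (2.4) |
|---|---|---|---|---|
| 1 | yes | yes | no | not listed |
| 2 | yes | yes | no | yes |
| 3 | yes | yes | no | yes |
| 4 | none stated | not listed as aware | yes | yes |

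Rows 1 and 4 are the wrong way round for concealment.

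**2. How much a known block of 12 gives away**

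Inputs: four arms in equal ratio and a block of 12, so three places per arm; 169 patients (section 5.1). The listed stratum levels give 3 × 3 × 2 = 18 strata, or 169/18 = 9.4 patients each. The stated 12 strata give 169/12 = 14.1 each.

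At each position the best guess is the arm with most places left. Its chance of being right is (most places left in any arm)/(places left in the block), averaged over all possible histories. For example:

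- Position 1: 3/12 = 25%.
- Position 2: 3/11 = 27%.
- Position 4: three draws always leave at least one arm untouched, so 3/9 = 33%.

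The full enumeration gives:

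| Position | Best guess right | At least one arm used up | Next arm certain |
|---|---|---|---|
| 1 | 25% | 0% | 0% |
| 4 | 33% | 2% | 0% |
| 7 | 39% | 36% | 0% |
| 9 | 48% | 84% | 0% |
| 10 | 51% | 100% | 2% |
| 11 | 59% | 100% | 18% |
| 12 | 100% | 100% | 100% |
| Mean of 1 to 12 | 44% | 42% | 10% |
| Mean of 1 to 9 | 35% | 23% | 0% |

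Check on the 10%: the next arm is certain at position 12 always, at position 11 with chance 2/11, and at position 10 with chance 2/11 × 1/10. So (1 + 0.182 + 0.018)/12 = 0.100.

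The full-block means overstate the leak, because many blocks would not fill. Weighting each position by the chance that a stratum reaches it (169 patients, strata equally likely, allocations learned one at a time) gives:

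| Strata | Best guess right | At least one arm used up | Next arm certain |
|---|---|---|---|
| 18 (listed levels) | 37.5% | 27% | 3.2% |
| 12 (stated) | 40.4% | 33% | 6.7% |

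Simulations in which allocations became known in batches of 1, 2 or 4 (an assumed stand-in for weekly randomization) gave 37 to 38% for 18 equal strata and 40 to 41% for 12. The next arm was certain for about 3% and 6 to 7% of patients. An uneven set of 18 strata gave about 37% and 4%.

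**Scale at one site.** If hospitals recruit equally and each has one researcher, Researcher 1 screens about 169/3 = 56 patients. The extra correct guesses are 56 × (0.37 − 0.25) = 7 to 56 × (0.41 − 0.25) = 9. The certain ones are 56 × 0.03 = 2 to 56 × 0.07 = 4.

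**The case against.** **Researcher 1's knowledge is not stated.** A reader might infer that Researcher 1 knows the block size. No section says so; it follows only from absence from a list. Since Researcher 4 could hardly be blind, the list may be misnumbered, with 1, 2 and 3 intended. This stands: the text shows a defective rule, not a breach of concealment.

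**A fixed size of 12 is one reading.** The section also speaks of varying sizes, and every figure above assumes fixed blocks of 12. This stands too. What is certain is that the two statements conflict.

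**There are safeguards.** Consecutive enrolment rules out picking among eligible patients, and weekly randomization delays knowledge of the latest allocations. Both are partial. Consecutive enrolment does not govern the judgement of who is eligible, and batches of 2 or 4 barely change the figures. No recruitment rate is given, so it is not known how often two patients from one stratum fall in the same week.

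**Screeners have limited discretion.** Distress is scored from patient-completed questionnaires against fixed cut-offs. Ulcer duration is on a form completed by the physician or nurse, and transplant, hemodialysis and cancer are matters of record. This narrows the room for steering. It does not close it, because data are collected in face-to-face interviews and the screeners apply the criteria.

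**The largest figures seldom apply.** A reader might take 44% correct and 10% certain as the size of the problem. Those hold only for blocks that fill, and with about 9 patients per stratum many would not.

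**Conclusion.** The point holds as a badly set and self-contradictory rule in section 2.4. Followed literally, it leaves one unblinded screener without the stated protection, names the sequence builder as blind, and gives two incompatible accounts of the block sizes. This is not detail that an article may leave to the full protocol, because the rule is stated and the statement is wrong.

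The size is moderate. A screener who knew the blocks were fixed at 12 and knew the past allocations in the stratum would predict the next arm about 37 to 41% of the time instead of 25%. The next arm would be certain for about 3 to 7% of patients. These figures assume that the list is literal, that every block is 12, and that strata are about equally filled (one uneven pattern gave similar results). The documents do not support a claim that allocation was fully predictable, that Researcher 1 in fact knew the block size, or that entry was steered.

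**What to change.** In section 2.4:

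- State that Researchers 1, 2 and 3, and anyone else who screens or enrols, are blind to block sizes.
- Have Researcher 4, who has no stated screening role, choose and hold the block sizes, and remove Researcher 4 from the blinded list.
- Use randomly varying sizes in multiples of four and do not disclose them to the sites.
- Reconcile the statement on varying blocks with the single size of 12.

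Section 7 describes compliance difficulties already met, so the trial appears to be under way. If recruitment is still open, apply the new sizes only to later blocks in each stratum, so that part-filled blocks are not abandoned. If Researcher 1 did know the block size, report this as a limitation.

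The cost is a wording change and a new list for later blocks. The downsides are slightly looser balance between arms and Researcher 4 having to hold the list. A separate log of eligibility before each weekly release would add little: Table 1 already places eligibility and consent before allocation, and a log does not stop someone predicting the arm before declaring a patient eligible.

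### The listed stratification levels give 18 strata, not the stated 12, so a block of 12 exceeds the average stratum and balance is weaker than the protocol implies

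*Protocol article*

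**What the plan says.** All of the following is in the protocol article.

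- **Strata (2.4).** "A priori stratification was defined considering the three hospitals where data collection will take place", together with CKD in three levels, "without CKD/CKD stage 1 and 2/CKD stage 3 and 4", and two levels of "PAD (without PAD/with PAD". The section then gives the result as "in a total of 12 possible strata". The stated purpose is that the stratification should ensure balance between the groups on confounders.
- **Blocks (2.4).** Patients are assigned to four groups "in varying size blocks so that, over time, all groups can have a similar number of participants". Two lines later the sequence is described as "with a 1:1 allocation, using random block sizes of 12".
- **Who knows what (2.4).** Researcher 4 creates the sequence, yet "Researchers 2, 3, and 4 are blind to the block size used in the randomization procedure". Researchers 1, 2 and 3 are aware of allocations and, under 2.3, also identify eligible patients.
- **Eligibility (2.3).** Transplant and haemodialysis are exclusions. CKD stage 5 as such is not.
- **Design label (2.2).** "longitudinal, participant-blinded, sham-controlled, cluster randomized controlled trial (RCT".
- **Size (5.1).** 169 participants, 42 per group.

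**The concern.** The stated number of strata does not follow from the levels listed in the same paragraph. That matters beyond the typing of a number. The count tells the team how many allocation lists must exist, and it sets the number of patients per list against which a block size is chosen. A block of 12 looks reasonable if there are 12 strata, because the average list then runs past one full block. It fits poorly if there are 18.

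Four neighbouring statements need attention for the same reason, namely that the scheme cannot be carried out exactly as described. One group of eligible patients fits no CKD level. The blocks are both variable and of one size. The person who builds the sequence is said not to know the block size. The trial is labelled cluster randomised although patients are the units allocated.

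**Working it through.** **1. Strata count.** The inputs are the levels in 2.4: hospitals 3, CKD 3, PAD 2.

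3 × 3 × 2 = 18. The stated 12 is not reproduced.

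Twelve is reached with two hospitals (2 × 3 × 2) or two CKD levels (3 × 2 × 2). Both contradict the levels that the section lists.

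**2. Patients per stratum.** N = 169 (5.1).

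- With 18 strata: 169 / 18 = 9.4
- With 12 strata: 169 / 12 = 14.1

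Only the second exceeds one block of 12.

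**3. How often a block completes.** If the 18 strata are equally common, the number of patients in a stratum is Binomial(169, 1/18). P(at least 12) = 0.231, so about 18 × 0.231 = 4.2 strata complete a block.

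**4. Balance, by simulation** (3,000 trials per row, four arms at equal ratio, fixed block size). The article gives no prevalences, so the unequal splits are assumptions. Split A is hospitals 50/30/20%, CKD 60/20/20%, PAD 50/50%. Split B is the same with equal hospitals. Gap means largest minus smallest arm over the whole trial.

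| Scheme | Shares | Strata completing a block | Patients in completed blocks | Mean gap (95th percentile) | Chance of gap ≥ 8 |
|---|---|---|---|---|---|
| 18 strata, blocks of 12 | equal | 23% | 30% | 6.3 (11) | 31% |
| 18 strata, blocks of 12 | A | 27% | 44% | 6.7 (12) | 36% |
| 18 strata, blocks of 12 | B | 32% | 43% | 7.1 (13) | 40% |
| 18 strata, blocks of 4 | all three | 81–99% | 84% | 3.9–4.0 (7) | 3% |
| Simple randomisation | all three | – | – | 13.2–13.4 (23–24) | 84–85% |
| 12 strata, blocks of 12 | equal | 76% | 65% | 4.95 (9) | 12% |

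With 18 strata and blocks of 12, in 11–21% of strata an arm is empty although the stratum has at least four patients.

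A separate run of 4,000 trials used another assumed split (hospitals 40/35/25%, CKD 50/25/25%, PAD 50/50%):

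- Blocks of 12: 37% of patients in completed blocks, gap 6.7 (12), chance of 8 or more 36%.
- Mixed blocks of 4 and 8: 69%, gap 5.0 (9), chance 12%.

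**5. Cost in precision.** For a two-arm contrast, relative efficiency is 4·n₁·n₂ / (n₁ + n₂)².

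- 38 v 45 (gap 7): 4 × 38 × 45 / 83² = 0.993
- 36 v 48 (gap 12): 4 × 36 × 48 / 84² = 0.980

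**6. Textual checks.**

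- CKD: a stage 5 patient not on haemodialysis passes 2.3 but matches none of the three levels in 2.4.
- Blocks: a single size of 12 is not varying, and a 1:1 ratio does not describe four arms.
- Concealment: whoever generates blocks of a given size ordinarily has to know that size.
- Label: 2.4 allocates individual patients within hospitals, and 5.1 contains no allowance for clustering.

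**The case against.** The best defence accepts the miscount and disputes the harm.

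- **Balance.** Within any stratum two arms can differ by at most 3, because a block of 12 holds three per arm. The overall gap is about half that of simple randomisation, and step 5 shows that precision hardly suffers. This stands. A reader might infer that the purpose of the stratification is largely lost, but the figures do not support that.
- **Assumptions.** The simulated results rest on assumed shares and a fixed block of 12. If the blocks really vary, those figures do not apply. This stands, and it is a reason to state the block sizes unambiguously.
- **Predictability.** Foreknowledge in a block of 12 arises mainly near its end, which most strata do not reach. Weekly batch randomisation also makes single allocations harder to guess, and smaller blocks are if anything easier to guess. This stands as a cost of the change to the blocks.
- **Analysis.** Section 5.2 already adjusts for baseline ulcer stage and will consider other clinical confounders, which limits the consequences of chance imbalance.
- **Timing.** The Discussion speaks of difficulties already experienced, so the trial appears to be under way. Changing only the unused lists would bring less than the simulated gain.
- **Condensed article.** The full protocol may say where stage 5 patients go. That is possible, but the levels printed in 2.4 are presented as the complete set.

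None of this rescues the figure of 12 or the conflicting descriptions.

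**Conclusion.** The stated number of strata is wrong as written: it is 18 on the section's own levels, and this needs no assumption. The mean stratum of 9.4 patients, at the planned 169, is therefore smaller than one block of 12. About a quarter to a third of strata would complete a block, and arm sizes would differ by about 6–7 on average against a plan of 42 per arm. That is too loose for a scheme said to ensure balance, but it remains clearly better than simple randomisation and costs only about 1–2% in efficiency. These magnitudes depend on the illustrative shares and the fixed block size. The mean stratum size would rise if the sample size were increased.

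The stage 5 gap, the two block descriptions, the statement on the sequence generator and the cluster label are textual faults that hold regardless. How many stage 5 patients are affected is unknown.

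Two further inferences are tempting and are not supported. One is that only 12 lists exist and six combinations have none: the article does not say how many lists were made, and 12 may simply be a miscount. The other is that Researcher 1 can anticipate allocations: that researcher is merely absent from the list of those blind to block size, and the article does not say that the size was disclosed.

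**What to change.** 1. In 2.4, change the count to 18, or define the levels that give 12. Check the actual lists and confirm that one exists for every combination.
2. Extend the CKD stratum definition so that every patient eligible under 2.3 falls in exactly one level.
3. Give one description of the blocks and write the ratio as 1:1:1:1. For lists not yet used, generate randomly mixed smaller blocks, for example 4 and 8. Leave lists already in use as they are.
4. State that block sizes are concealed from Researchers 1–3, who recruit and know past allocations. Correct the statement that Researcher 4, who generates the sequence, is blind to block size.
5. Delete the word cluster from 2.2.

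The cost is a short text correction, a check of the lists and regeneration of the unused ones. The downside is that smaller blocks are slightly more predictable to researchers who see allocations. Random mixing and concealment of the sizes reduce that risk but do not remove it.
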